## Introduction

1

The effects of physical activity (PA) on academic achievement (1, 2), movement behaviors (3, 4) and health outcomes such as body mass index [BMI; (5, 6)], aerobic fitness (7, 8), and psychological health such as stress/ test anxiety levels (9, 10) among school children have been long established. However, reports including the elementary education sector highlighted that children should meet the recommended daily PA behavior levels, such as engaging in at least 60 min of moderate-to-vigorous physical activity [MVPA; (11)]. One primary factor influencing this figure is that children have long seated learning time in the classroom due to high academic curriculum demands in primary school (12, 13). As a result, sedentary behavior among primary school children has become alarming, with figures steadily increasing worldwide (14, 15).

A situation analysis conducted in 2016 showed that the learning time is less activity-based (16) in Sri Lanka. National surveillance data also indicated that 63 to 72% of students (age range = 6–12 years old) engaged in sedentary activities (17). Among the five grades in primary schools in Sri Lanka, the grade five curriculum is one of the most loaded and competitive in teaching and learning (18–20). The underlying reason is that grade five students are expected to sit for a national-level competitive scholarship examination in addition to their curriculum-related reviews at the term tests (18, 19, 21, 22). Therefore, the teachers and students are tense in preparing for the scholarship examination and surpassing the cutout marks while achieving the required competency levels for fifth graders (16, 19, 23, 24). This has increased the sedentary behavior with more traditional seated learning as the main objective of the teachers is to improve the students’ academic achievement. As a consequence, most of the fifth graders are identified to be physically inactive (17, 25–27), below recommended body mass index (BMI) percentiles (17, 25), aerobically unfit (18), and stressful (16, 19, 20, 23, 24, 28). Therefore, there is a need to target fifth graders in primary schools in Sri Lanka to prevent grade-related sedentary behavior and obtain health benefits and maximum academic performance.

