##### Mathematics achievement

2.3.1.1

Mathematics achievement will be evaluated through a curriculum-based standardized test designed by the teaching officers experienced in Grade five mathematics performance-related evaluation. This test will consist of 60 questions to assess the expected performance of a given term. Students will complete the test within 45 min. The principal investigator and the classroom teacher will collaboratively administer the test.

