##### Health outcomes (BMI, aerobic fitness, perceived stress)

2.3.2.2

Students’ weight in kilograms to the nearest 0.1 kg (27, 63, 64) and height in centimeters to the nearest 0.1 cm (27, 63, 64) will be recorded using a standard stadiometer and a weighing scale. Body weight in kilograms will be divided by height in meters squared to measure the BMI (27, 63, 64). Students’ age and gender-specified BMI categories will be identified using the calculator introduced by the Ministry of Health in Sri Lanka (65).

The multistage shuttle run/ beep test [66] will be used to measure aerobic fitness, proven highly reliable and valid among school children (32, 66). Results from the test will be used to calculate VO_2_ max using the equation proposed by previous studies (67, 68). Students will be asked to run back and forth on a 20 m course as instructed by a sound signal emitted from a pre-recorded tape, ensuring they touch the 20 m line with their foot (32). The sound signal frequency increases by 0.5 km/h every minute, indicating the next stage (level), starting with a speed of 8.5 km/h. The test ends when participants fail to reach the line before the signal.

Perceived stress will be measured using a translated Sinhala version of the Perceived Stress Questionnaire 8–11 (PSQ8-11 (67)). PSQ8-11 will measure two subscales: perceived psychological stress (nine questions) and physiological stress (10 questions). This 19-item questionnaire requires the students to recall their feelings from the previous week. The students will self-rate their responses on a four-point Likert scale (1 = never, 2 = sometimes, 3 = often, 4 = very often). A higher score on the questionnaire will indicate greater perceived stress (67).

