### Data analysis

2.6

Data will be statistically analyzed using IBM SPSS software version 28. A randomization check will be performed using independent t-tests (for continuous outcomes) and chi-square (for categorical variables) tests (70). Descriptive statistics such as mean, standard deviation, and percentages will be used to describe the baseline characteristics of the sample and the attrition rates. Primary analysis will be handled with an intention-to-treat modified (m-ITT) approach (71). Missing values analysis will be conducted to observe whether the data are missing completely at random (MCAR). Missing data values will be handled using the multiple imputation method with chained equations.

To test the effectiveness of the IcPAB, generalized linear mixed models (GLMM) will be used by linking to the dependent variables at the individual level (students) and group level (intervention vs. control) with time (pre to post-test) (12, 72, 73). A random intercept will be used to account for the repeated measures of the subjects (35). To test the moderation effects by gender, an interaction test will be conducted via GLMM by setting group-by-time-by-gender as the moderator (35). A 5% level (two-tailed) will be used as the statistical significance cut-off point (74). All the intervention effects will be reported based on the type III tests of fixed effects of GLMM. The estimates of the impact sizes will be written based on the estimated coefficients (*β*) with the 95% confidence intervals/ odds ratio for those estimates based on previous intervention effect report practices for IcPAB (31, 63) in addition to the mean changes in the intervention and control groups. The odds ratio (OR), where OR = 1.68, 3.47, and 6.71 are equivalent to Cohen’s *d* = 0.2 (small), 0.5 (medium), and 0.8 (large), will be used for the interpretations, respectively, (75). Furthermore, a sensitivity analysis to the m-ITT results will be facilitated by considering all the subjects who complete all the baseline and post-test measurements for all the primary and secondary outcomes to ensure the robustness of the primary data assessment and strengthen the conclusions and credibility of the study’s findings.

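### The odds-ratio cut-offs 1.68/3.47/6.71 match d = 0.2/0.5/0.8 only at a reference proportion of about 1%, and an odds-ratio scale does not fit the continuous primary outcomes

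*Protocol article*

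**What the plan says.** Section 2.6 (Data analysis) plans generalized linear mixed models with a random intercept for the repeated measures on each child. Effects are to be reported as coefficients "with the 95% confidence intervals/ odds ratio for those estimates", alongside mean changes in each arm. The grading rule follows: odds ratios of "1.68, 3.47, and 6.71 are equivalent to Cohen’s" d of "0.2 (small), 0.5 (medium), and 0.8 (large), will be used for the interpretations". No reference proportion is attached to the equivalence, and the rule is not limited to categorical outcomes.

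The outcomes are set out in section 2.3:

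- **Mathematics** (primary) is a test score: "This test will consist of 60 questions to assess the expected performance of a given term".
- **Reading** (primary) comes from a timed reading test.
- **Secondary outcomes** are mostly quantities or scores: accelerometer measures, BMI, VO2 max from the shuttle run, and a 19-item stress questionnaire.
- **BMI category** is the evident categorical variable: "Students’ age and gender-specified BMI categories will be identified using the calculator introduced by the Ministry of Health in Sri Lanka". The article gives no proportion for any category and does not say whether the category or BMI itself will be modelled.

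**The concern.** The odds ratio that corresponds to a given standardised difference is not a constant. Under a normal-threshold model it depends on the proportion in the reference group. Under a logistic model it does not, but it then takes one fixed set of values, and those are not the values stated. A conversion given without its condition is therefore either a special case or an error.

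At stake is the pre-specified rule that decides whether a result is called small, medium or large. If the cut-offs do not correspond to the d values they are tied to, the published labels will not mean what readers take them to mean. The two primary outcomes raise a second problem. A test score analysed on its own scale yields a mean difference, not an odds ratio, so the rule has nothing to act on.

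**Working it through.** **Inputs.** From section 2.6: odds ratios 1.68, 3.47 and 6.71, and d = 0.2, 0.5 and 0.8. The article gives no reference proportion p and no within-child correlation, so both are treated below as assumptions and shown as ranges.

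**1. Reproducing the stated figures.** Shift a normal threshold by d: q = Φ(Φ⁻¹(p) + d), and OR = [q/(1 − q)] / [p/(1 − p)].

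At p = 0.01, Φ⁻¹(p) = −2.326 and the reference odds are 0.01/0.99 = 1/99.

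| d | q | OR = 99·q/(1 − q) | stated |
|---|---|---|---|
| 0.2 | 0.01674 | 1.685 | 1.68 |
| 0.5 | 0.03390 | 3.474 | 3.47 |
| 0.8 | 0.06346 | 6.708 | 6.71 |

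With q rounded to four decimals (0.0167, 0.0339, 0.0635), the results are 1.681, 3.474 and 6.713, which round to the stated figures. Solving each stated OR for p gives 1.05%, 1.01% and 1.00%. At p = 2% the values are already 1.61, 3.13 and 5.75, and no other proportion tried gives all three. That the cut-offs were built on 1% is inferred from this match; the article does not say so.

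**2. Marginal odds ratios at other proportions (assumed).**

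| p | d = 0.2 | d = 0.5 | d = 0.8 |
|---|---|---|---|
| 10% | 1.46 | 2.50 | 4.14 |
| 30% | 1.39 | 2.24 | 3.63 |
| 40% | 1.38 | 2.23 | 3.63 |
| 50% | 1.38 | 2.24 | 3.72 |
| 70% | 1.40 | 2.38 | 4.20 |

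Over the whole span from 10% to 70%, the ranges are 1.38–1.46, 2.23–2.50 and 3.62–4.20. The logistic conversion, OR = exp(d·π/√3), needs no p and gives 1.44, 2.48 and 4.27.

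Read back the other way, the stated cut-offs correspond to d = 0.28–0.32, 0.69–0.77 and 1.03–1.17 over the same span, and to 0.29, 0.69 and 1.05 by the logistic conversion. A marginal effect of exactly d = 0.5 would be called small, and one of exactly d = 0.8 would be called medium.

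**3. Conditional odds ratios from the planned model.** A logistic model with a child-level random intercept of variance σ² gives a child-specific OR. If d is scaled by the total latent SD and ρ is the within-child latent correlation, σ² + π²/3 = (π²/3)/(1 − ρ), so OR = exp[d·(π/√3)/√(1 − ρ)].

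| ρ (assumed) | d = 0.2 | d = 0.5 | d = 0.8 |
|---|---|---|---|
| 0 | 1.44 | 2.48 | 4.27 |
| 0.3 | 1.54 | 2.96 | 5.67 |
| 0.5 | 1.67 | 3.61 | 7.78 |
| 0.7 | 1.94 | 5.24 | 14.14 |

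The stated cut-offs are met at ρ of about 0.51, 0.47 and 0.42 respectively. Below those values they are too high and effects are graded too small. Above them they are too low and effects are graded too large.

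**4. Continuous outcomes.** For mathematics, reading and most secondary outcomes the planned model returns a coefficient in the units of the measure. It can be placed on the d scale directly by dividing by a standard deviation. No odds ratio arises.

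**The case against.** A reader might infer that this trial's effects will be graded too small. The documents do not support that. It holds for marginal odds ratios over a wide range of proportions, but the planned model yields conditional ones. A BMI category measured twice about 13 weeks apart could have a within-child correlation above 0.5, which would reverse the direction. The same gap means that converting a random-intercept odds ratio by ln(OR)·√3/π would overstate d. This objection stands.

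The introduction may also seem to supply a base rate: "National surveillance data also indicated that 63 to 72% of students". That figure concerns sedentary activity, which the trial measures by accelerometer, and says nothing about the proportion in a BMI category. The introduction's remark that most fifth graders fall below recommended BMI percentiles is qualitative. The proportions used above are therefore assumptions.

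Nor does the plan leave the primary outcomes without usable results. Section 2.6 already provides coefficients with confidence intervals and mean changes by arm, and it names the d anchors. Mislabelling is not uniform either: the planning effect, f = 0.21 or d = 2 × 0.21 = 0.42, corresponds to a marginal OR of about 1.96–2.17 at proportions of 10% to 70% and is called small under the stated cut-offs and under the corrected ones.

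Finally, it is not certain that any outcome will be graded by odds ratio, and the source cited for the cut-offs may state the 1% condition. Neither point makes the sentence in the article correct.

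**Conclusion.** The point holds as a false general equivalence in a pre-specified interpretation rule. The three cut-offs correspond to d = 0.2, 0.5 and 0.8 at a reference proportion of about 1%. The article omits that condition, and no outcome is described as so rare. The stated figures exceed the marginal equivalents at 10% to 70% by roughly 15–22%, 39–56% and 60–85% (1.68/1.46 to 1.68/1.38; 3.47/2.50 to 3.47/2.23; 6.71/4.20 to 6.71/3.62). For the conditional odds ratios of the planned model the size and sign of the error depend on a correlation that the article does not give, so no direction can be claimed for this trial. Separately, the rule cannot be applied to either primary outcome or to most secondary outcomes, which are continuous.

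The consequence is limited to the words small, medium and large. The "A 5% level (two-tailed) will be used as the statistical significance cut-off point" is untouched, as are the estimates, their intervals, the power and the sample size.

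**What to change.** In section 2.6:

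- Delete the three odds-ratio cut-offs.
- For mathematics, reading and the other continuous outcomes, divide the group-by-time estimate already planned, and its 95% confidence interval, by the pooled baseline SD. Grade the result against d = 0.2, 0.5 and 0.8.
- For any categorical outcome, report the odds ratio with its 95% confidence interval and the proportions in each group, without these labels.

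This replaces one sentence. It needs no new data, no change of model and no change to the sample size. The only added computation is one division per continuous outcome.

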### Study design and selection of subjects

2.1

A single-blinded parallel randomized controlled trial (RCT) will evaluate the intervention effects of IcPAB compared to a control group. Target participants will be the fifth graders in government primary schools. Based on the data shared by the Ministry of Health, Sri Lanka, the COVID-19 pandemic severity was slight in the Bandarawela Education Zone (city) in Badulla District. Therefore, the government schools of Bandarawela Education Zone were contacted to initiate the recruitment process in late 2022. The age range of the grade five students is 9 to 10 years old. The targeted population is exposed to 6 hours of regular classroom time (7.30 a.m. to 1.30 p.m.), including a 20-min lunch break according to the government primary school norms in Sri Lanka. Within the government primary school setting, the teacher in charge of a class should teach all subjects in the syllabus for the class, such as mother tongue, mathematics, religion, environment and English. Depending on the interests of the schools, the teachers will conduct additional classes after regular school time to prepare the students for the year-end national scholarship examination. Therefore, the study was designed to be implemented only during the standard classroom time for 12 weeks.

Based on GPower 3.1 software, through *a priori* power analysis, it was estimated to obtain at least 198 participants for both the intervention and control groups to expect an effect size of 0.21 [Cohen’s *f*, converted from *d*, (45, 46)] on academic achievement (mathematics) by providing a power of 0.8 (1-β) with an alpha of 0.05 to test the primary hypotheses of the study with an estimated 10% dropout rate [dropout rates were less than 10% in previous studies (10, 33, 47)] at the post-test/ follow-upstage.

Therefore, it is anticipated to recruit five to six classes (30 to 40 students per class) from two government schools to conduct the study to reach the required minimum sample size. Block randomization technique via MS Excel, will be used to randomize the sample classes by an assessor who is blinded to the intervention content and outcome assessment.

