## Discussion

3

The primary aim of this RCT is to investigate the effects of the IcPAB program on the mathematics and reading achievement of fifth graders in Sri Lanka. Secondarily, the intervention effects of the LPA, MPA, VPA, MVPA, steps count, and sedentary behavior will be evaluated in addition to the health outcomes such as BMI, aerobic fitness, and perceived stress.

This intervention has addressed several recommendations and limitations pointed out by previous studies: (1) To the best of the authors’ knowledge, this is the first IcPAB intervention, which will be implemented among governmental primary school girls and boys in Sri Lanka by integrating mathematics and reading curriculum components into the IcPAB content. The intervention will analyse its moderation effects by gender. Thus, this intervention’s findings will fill an existing population gap and add new knowledge to academia (39, 41). (2) It is reported that the IcPAB, which requires a more prolonged duration per activity, are less feasible (12, 39, 76). At the same time, teachers prefer shorter bouts of IcPAB, at least at most 5 minutes (20, 37). This intervention will provide more evidence of the effects of using five-minute curriculum-integrated PA breaks.

(3) The intervention uses a RCT with a parallel single-masked design, ensuring a low bias risk to its methodological quality (39, 41, 44). Also, the protocol contains a precise data analysis plan for handling missing data and examining the data with a sensitivity analysis. (4) Intervention fidelity and process evaluation mechanisms will be systematically followed and reported to ensure the feasibility of the RCT in the ‘real-world’ context (12, 39). As for the primary outcome evaluations, curriculum-based measurements are designed. Curriculum-based measures were recommended by the previous researchers due to its sensitivity toward small changes (12, 39) and the ability to be administered frequently (12, 39).

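### The completer analysis does not test the missing-at-random assumption behind the imputed mathematics and reading results, so it cannot show that they are robust

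*Protocol article*

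**What the plan says.** Section 2.6 (Data analysis) sets a modified intention-to-treat primary analysis with multiple imputation by chained equations. It also plans a look at whether data are missing completely at random (MCAR), but ties no change of method to the answer. One sensitivity analysis is named: "a sensitivity analysis to the m-ITT results will be facilitated by considering all the subjects who complete" all baseline and post-test measurements on every primary and secondary outcome. Its stated purpose is "to ensure the robustness of the primary data assessment and strengthen the conclusions and credibility" of the findings. Section 3 (Discussion) counts this as a strength: "the protocol contains a precise data analysis plan for handling missing data and examining the data with a sensitivity analysis". The Introduction lists missing-data handling among the weaknesses of earlier trials.

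The figures used below come from section 2.1: "it was estimated to obtain at least 198 participants for both the intervention and control groups", "to expect an effect size of 0.21" (Cohen's f), "by providing a power of 0.8 (1-β) with an alpha of 0.05", and "with an estimated 10% dropout rate". Section 2.6 adds: "A 5% level (two-tailed) will be used as the statistical significance cut-off point".

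**The concern.** A sensitivity analysis should relax the assumption that carries the primary result. Here that assumption is missing at random (MAR): pupils without a post-test score would have scored like pupils in the same arm with similar observed data. Removing the incomplete pupils does not relax it. If low scorers are lost in one arm for reasons not captured by the observed data, both analyses are biased, and they may agree.

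Loss that differs by arm is plausible. Section 2.2.2 lets parents, children and teachers withdraw permission at any time, and only intervention classes have activities to deliver. Whole classes are randomized, five or six in all, so losing one removes about 17% to 20% of pupils (1/6 to 1/5). At stake is a robustness claim for the two primary outcomes that the named analysis cannot support.

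**Working it through.** **1. The plan's own sample size.** f = 0.21 with two equal groups gives d = 2f = 0.42. Per arm, n = 2(1.960 + 0.842)²/0.42² = 2 × 7.85/0.1764 ≈ 89, so 178 in total. 178/0.90 = 197.8, rounded up to 198, which is the stated figure. The exact two-group F test gives 180, and 180/0.90 = 200. Equal allocation is assumed; the article gives no ratio.

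**2. What each analysis needs.** Imputation with arm and baseline in the model needs MAR. Completers in a group-by-time model, where baseline is a response and not a covariate, are valid under MCAR, or if loss depends only on covariates in the model. Neither is valid in general if loss depends on the unseen post-test score (MNAR).

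**3. Simulation.** 198 independent pupils, true effect 0.42 SD, 1,500 runs per scenario; the estimate is the group difference in pre-post change. Assumed, because the article gives no values: pre-post correlation 0.7 and a log-odds slope for dropout of 1.5 per SD. Under MAR, dropout depends on baseline, in opposite directions by arm. Under MNAR, low post-test scorers are lost in the intervention arm and loss in the control arm is random.

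| Mechanism | Missing | Imputation | Completers |
|---|---|---|---|
| MCAR | 10% | 0.424 | 0.425 |
| MAR | 10% | 0.420 | 0.347 |
| MAR | 20% | 0.420 | 0.283 |
| MNAR | 10% | 0.487 | 0.459 |
| MNAR | 20% | 0.543 | 0.489 |
| MNAR | 30% | 0.600 | 0.520 |

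Under MNAR both estimates are too high. At 10% missing they differ by about 0.03 SD, roughly a quarter of the standard error of 0.115 SD derived in step 4, so they would be read as agreeing. Under MAR they differ although imputation is right. With no true effect, MNAR at 20% gives 0.118 and 0.065.

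**4. How large the unseen departure must be.** If a fraction p of the intervention arm is imputed and the true scores lie δ below the imputed ones, the estimate falls by pδ. Significance is lost when δ = (estimate − critical difference)/p. Pupils are treated as independent.

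- Post-test comparison, 180 analysed: SE = 2/√180 = 0.149; critical difference = 1.973 × 0.149 = 0.294. At 0.42 the margin is 0.126, so at p = 0.10, δ = 1.26 SD.
- Pre-post change, correlation 0.7: SE = 0.149 × √(2 × 0.3) = 0.115; critical difference about 0.228; margin 0.192; δ about 1.9 SD. At correlation 0.5 the factor is 1 and δ is again 1.26 SD.
- 20% missing, post-test comparison: SE = √(4/158.4) = 0.159; margin 0.42 − 1.96 × 0.159 = 0.109; δ = 0.109/0.20, about 0.54 SD.
- One of an assumed three intervention classes missing (p = 1/3), post-test comparison. With 60 against 90 observed, SE = √(1/60 + 1/90) = 0.167 and δ is about 0.27 SD. With 66 against 99, SE = 0.159 and δ is about 0.32 SD.
- Borderline estimate of 0.30 SD, 10% missing, post-test comparison: margin 0.006, δ about 0.06 SD.

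**The case against.** The strongest reply is that this asks for an extra analysis of a kind usually left to a statistical analysis plan, and that none is shown. That stands in part: a reader might infer that the trial has no other sensitivity analysis, but the article shows only that it names one. It does not dispose of the point, because the article itself chooses the completer analysis and states what it will establish.

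Second, a reader might infer that completers always need MCAR and always fail before imputation does. Neither is supported. Completers can be valid when loss depends only on model covariates, and in the MNAR scenario above they were less biased than imputation (0.459 against 0.487 at 10%, truth 0.42).

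Third, the completer analysis has some use: it shows whether the conclusion depends on the imputation, including a poor imputation model. That stands, and is a reason to keep it as supportive.

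Fourth, the small tipping values come from chosen scenarios. Any estimate just above the significance threshold tips easily, whatever the plan. The article does not say how the five or six classes divide between arms. A teacher who declines to run the activities need not lose the pupils' test scores. These points limit the size of the concern, not its logic.

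**Conclusion.** The point holds in a limited form. The named check does not do the job that section 2.6 gives it: it leaves MAR untested, can agree with the primary analysis when both are biased, and can disagree when the primary analysis is right. The planned MCAR assessment does not fill the gap, since it cannot separate MAR from MNAR.

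A reader might go further and infer that the expected primary result is fragile. The documents do not support that. At the planned 10% dropout and the planned effect, the unseen departure would have to be about 1.3 SD (post-test comparison) to 1.9 SD (change, correlation 0.7). The concern becomes material if a class is lost (about 0.3 SD) or the estimate is borderline.

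These sizes assume equal planned arms and independent pupils. Ignoring class clustering makes them optimistic, while a pre-post correlation above 0.5 works the other way in the change analysis. The correlation and dropout slope in the simulation are assumptions. That completers do not test MAR does not rest on them.

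**What to change.** In section 2.6, prespecify a delta-adjusted (tipping-point) re-analysis of the same imputed data sets for mathematics and reading. Shift the imputed post-test scores downward in the intervention arm, for example in steps of 0.1 baseline SD until the conclusion changes, and once apply an equal shift in both arms. Re-run the same model at each step. Report the smallest shift that changes the conclusion beside the number missing per class and arm.

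Keep the completer analysis as supportive only. Remove the statement in section 2.6 that it ensures robustness, and align the Discussion's description of the missing-data plan.

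The cost is a constant added to values already imputed, a re-run of the model and one extra table; no new data are needed. The downside is that the result may look less robust than a completer analysis alone would suggest.

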**Methods:**

The study will adopt a randomized controlled trial (RCT), comprising an in-classroom physical activity breaks program group and a control group to evaluate the effects of IcPAB on academic achievement, movement behaviors and health outcomes. The intervention design is based on the capability (C), opportunity (O) and motivation (M) behavior (B) (COM-B) model. A least 198 fifth graders will be recruited from two schools in Uva province, Sri Lanka. The recruitment process will start in late 2022. Class teachers of the intervention group will implement 5-min activity breaks at least three times a day after completing a training session. The primary variables include mathematics and reading achievement. The secondary variables include physical activity levels, steps count, sedentary behavior, body mass index, aerobic fitness, and perceived stress. Data collection will be implemented at pre-test and post-test, respectively. Intervention fidelity and the process will also be evaluated.

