##### Movement behaviors

2.3.2.1

Objective data for the light physical activity (LPA), moderate physical activity (MPA), vigorous physical activity (VPA), MVPA, steps count, and sedentary behavior will be measured during regular school hours using waist-worn accelerometers (GT3-X triaxial model, ActiGraph LLC, Pensacola, Fla., USA). Accelerometer data will be collected for a week at baseline and the post-test (week 13).

The accelerometers will be distributed by the teachers to the students randomly on the first school day and collected back on the fifth school day of the week. The research team will demonstrate to the teachers and the students how the accelerometers should be worn on the first day. However, due to the limited number of accelerometers, this study will use a randomly selected subsample (n = 47) to collect data to measure all the movement behaviors following previous research practice (12, 34, 58, 59). After accelerometers are randomly distributed to the students on the first day, the teachers will prepare a list assigning each student to a specific numbered accelerometer to ensure that the same child wears the same device every day during all the data collection stages. Then, the research team will receive another version of the same list where the students’ anonymous identification number is related to the accelerometer. The classroom teacher will also record absent students assigned with an accelerometer, and a researcher assistant will verify the data during the school visits.

Based on previous research practices (12, 60), only the accelerometer data, which will be identified for wearing more than five school hours on at least one school day, will be included in the analysis for intervention effects (12, 60). Following the standard practices in the studies involving children, non-wear time will be defined as 20 min of consecutive zeros (12, 31, 61). Freedson cut points will be used to classify movement behavior intensities based on the data collected in 15-s epochs (12, 62). Due to the focus on in-school PA, a longer wear time is not deemed necessary for the current study, as recommended by recent scholars (63). To confirm in-school wear-time for valid days, a further visual check of each accelerometer profile will be undertaken (63). Therefore, research assistants will randomly visit the schools during the data collection week to ensure that the students wear the same device accurately during school hours.

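### The completer sensitivity analysis requires complete data on every outcome, so the accelerometer subsample caps the check on mathematics and reading at 47 of 198 students

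*Protocol article*

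**What the plan says.** - **Sensitivity set (section 2.6, Data analysis).** The modified intention-to-treat results are to be checked by "considering all the subjects who complete all the baseline and post-test measurements for all the primary and secondary outcomes". The stated purpose is to show that the primary assessment is robust. No other sensitivity analysis is named.
- **Which outcomes count (Abstract, Methods).** Mathematics and reading are the two primary outcomes. For the others the Abstract says: "The secondary variables include physical activity levels, steps count, sedentary behavior, body mass index, aerobic fitness, and perceived stress". The research questions in the Introduction and section 2.3.2 classify the outcomes in the same way.
- **Who has movement data (section 2.3.2.1, Movement behaviors).** The article says that, "due to the limited number of accelerometers, this study will use a randomly selected subsample", whose size it gives as 47, and every movement outcome comes from these students. Devices are worn for a week at baseline and again in week 13. Data are used only where there is evidence of "wearing more than five school hours on at least one school day, will be included in the analysis".
- **Missing data (section 2.6).** "Missing data values will be handled using the multiple imputation method with chained equations".

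The article does not exempt the accelerometer outcomes from the completeness rule, and it does not define completeness outcome by outcome.

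**The concern.** A student who was never given an accelerometer cannot have complete baseline and post-test data on all secondary outcomes. The completeness rule and the subsampling plan therefore combine to remove every such student from the check on mathematics and reading, even when both tests were taken on both occasions.

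A completer analysis is useful here because it shows how far the main result depends on the imputation of lost data. Under this rule, most exclusions have nothing to do with lost data. A difference from the main result would mix the effect of dropping imputed values with the chance variation that comes from discarding three quarters of the sample. A sound primary result could look fragile, and a real problem with the imputation could be hidden in wide intervals.

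**Working it through.** **Inputs.** Section 2.1: 198 students in total, Cohen's f = 0.21, power 0.80, alpha 0.05, dropout 10%. Section 2.6: two-sided test. Section 2.3.2.1: 47 students with accelerometers, read as the trial total because no split by arm is given. Equal arms are assumed throughout.

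**1. The planned sample size reproduces.** For two equal groups d = 2f = 0.42.
- n per arm = 2(1.960 + 0.842)² / 0.42² = 89.0, so 89 per arm and 178 in total.
- Allowing for dropout: 178 / 0.9 = 197.8, so 198.
- The exact t or F version gives 180, or 200 after dropout, which is close to the stated figure.

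**2. Size of the completer set as written.**
- Ceiling: 47 / 198 = 23.7%.
- Excluded by design: 198 − 47 = 151, and 151 / 198 = 76.3%.
- With the planned 10% dropout applied to the subsample: 47 × 0.9 = 42.3, about 42.
- Short wear time, absence, or a missing shuttle run or stress questionnaire would lower it further. If 80% of the 47 were fully complete, 47 × 0.8 = 37.6 would remain.
- Completers defined per outcome, for comparison: 198 × 0.9 = 178.2, about 178 for each test.

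**3. Precision for the planned effect.** Power is from the noncentral t at d = 0.42, as an unadjusted comparison of two groups. The 95% half-width in SD units is 1.96 × √(4/N).

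| N | Power | Half-width (SD) | d detectable at 80% power |
|---|---|---|---|
| 178 | 0.80 | 0.29 | 0.42 |
| 47 | 0.29 | 0.57 | 0.84 |
| 42 | 0.26 | 0.60 | 0.89 |

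The width ratio is √(178/47) = 1.95 at 47 students and √(178/42) = 2.06 at 42. At 37.6 students power is about 0.24.

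**4. Allowing for the baseline measurement.** The article gives no pre–post correlation, so ρ is an assumption. Baseline adjustment raises the standardized effect to d / √(1 − ρ²).

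| Assumed ρ | Power at N = 47 | Power at N = 178 |
|---|---|---|
| 0.5 | 0.37 | 0.90 |
| 0.7 | 0.51 | 0.97 |
| 0.8 | 0.65 | 0.996 |

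If the effect is instead a difference in change scores, with standardized effect d / √(2(1 − ρ)), power at N = 47 is 0.29, 0.44 and 0.61 for the same three values.

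**5. Other reading of the 47.** If 47 were per arm, which the article does not say, the ceiling would be 94 of 198 (47%), with unadjusted power about 0.52.

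**6. What is left out.** These figures ignore clustering by class, for which no intraclass correlation is given. Clustering would lower power at both sizes. It would lower it more in the full sample, which has more students per class, so the gap in effective information would be smaller than shown. The model in section 2.6 has a random intercept for the student only, so the intervals it reports would still differ by about the ratio in step 3.

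**The case against.** **The rule can be read more kindly.** The sentence might mean that a completer analysis is run for each outcome, on the measurements each student was due. The authors may well have intended this, and a full analysis plan could define the set properly. But the article does more than leave the detail open: it states a rule, and the rule asks for completeness on all outcomes together. A programmer who followed it would keep at most 47 students.

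**Three stronger readings are tempting, and the documents do not support them.**

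- *That the plan imputes movement outcomes for the 76% of students who had no device.* The imputation sentence in section 2.6 has no stated limit. However, section 2.3.2.1 confines the analysis of intervention effects on movement to valid recorded accelerometer data. The two sections leave an ambiguity to be cleared up, not a fixed plan to impute unmeasured students.
- *That the check would almost certainly be non-significant.* Power of 0.26–0.29 means a significant result in more than a quarter of trials if the planned effect is real. With baseline adjustment and ρ at the top of the assumed range, significance is more likely than not. In any case, a sensitivity analysis is judged mainly by whether its estimate agrees with the main one.
- *That the sensitivity result would be biased by subsampling, or that the primary result is undermined.* The 47 are chosen at random, so the subsampling itself does not select students by outcome. The main analysis of mathematics and reading does not use the completer set.

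These points limit the severity. They do not remove the conflict between the completeness rule and the subsampling plan.

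**Conclusion.** The rule is wrong as written, with moderate severity. The size of the cap follows from the article's own text and needs no outside assumption beyond reading 47 as the trial total. The power figures also assume equal arms and no clustering, and the adjusted ones depend on the assumed pre–post correlation. Across the range examined, power at 47 students stays well below that of a completer set defined per outcome. What is lost is precision and the ability to attribute a discrepancy to the handling of missing data. The sample size, the data collection and the primary analysis stand.

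**What to change.** Make two changes of wording in section 2.6, before the data are analyzed so that the completer set is not chosen after the results are seen.

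1. Define the completer set separately for each outcome, as the students with both a baseline and a post-test value on that outcome. Mathematics and reading then keep about 178 students each.
2. State that analyses of the movement outcomes, and any imputation of them, are confined to the 47 sampled students, and that students without a device are unmeasured by design and not missing. This brings section 2.6 into line with section 2.3.2.1.

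The cost is about two sentences. Data collection, sample size and the primary analysis do not change.
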